## **B: The MANUFACTURER's device is suspected to be a contributory cause of the INCIDENT**

In assessing the link between the device and the INCIDENT the MANUFACTURER should take account of:

- the opinion, based on available evidence, of healthcare professionals;
- the results of the MANUFACTURER's own preliminary assessment of the INCIDENT;
- evidence of previous, similar INCIDENTs;
- other evidence held by the MANUFACTURER.[L]  
[SEP]

This judgement may be difficult when there are multiple devices and drugs involved. In complex situations, it should be assumed that the device may have caused or contributed to the INCIDENT and the MANUFACTURERS should err on the side of caution.[L]  
[SEP]

## **C: The event led, or might have led, to one of the following outcomes:**

- death of a patient, USER or other person
- serious deterioration in state of health of a patient, USER or other person.[L]  
[SEP]

[figure not shown]

A serious deterioration in state of health can include (non exhaustive list):

- a) life-threatening illness,
- b) permanent impairment of a body function or permanent damage to a body structure,
- c) a condition necessitating medical or surgical intervention to prevent a) or b). [L][SEP]Examples:  
- clinically relevant increase in the duration of a surgical procedure, - a condition that requires hospitalisation or significant prolongation of [L][SEP]existing hospitalisation.
- d) any indirect harm (see definition under section 4.11) as a consequence of an [L][SEP]incorrect diagnostic or IVD test result or as a consequence of the use of an IVF/ART device when used within MANUFACTURER's instructions for use (use errors reportable under section 5.1.5.1 must also be considered).
- e) foetal distress, foetal death or any congenital abnormality or birth defects.

**NOTE :** [L][SEP]Not all INCIDENTs lead to death or serious deterioration in health. The non-occurrence of such a result might have been due to other fortunate circumstances or to the intervention of healthcare personnel.

It is sufficient that:

- ☐ an INCIDENT associated with a device happened, and
- ☐ the INCIDENT was such that, if it occurred again, it might lead to death or [L][SEP]serious deterioration in health. [L][SEP]

## 8.4 Incident Reporting Timelines

### Initial Report

**Serious public health threat:** IMMEDIATELY (without any delay that could not be justified) but not later than 2 calendar days after awareness by the MANUFACTURER of this threat.

**Death or UNANTICIPATED serious deterioration in state of health:** IMMEDIATELY (without any delay that could not be justified) after the MANUFACTURER established a link between the device and the event but not later than 10 elapsed calendar days following the date of awareness of the event.

**Others:** IMMEDIATELY (without any delay that could not be justified) after the MANUFACTURER established a link between the device and the event but not later than 30 elapsed calendar days following the date of awareness of the event.

In general, the report should be made to the National Competent Authority.

[figure not shown]

## Final Report

The MANUFACTURER shall provide a follow-up-report to the National Competent Authority if the investigation time reaches the time line given to the National Competent Authority within the initial report.

**Note for this study reporting to MHRA will be undertaken by the chief Investigator or designee as required by the protocol and national regulations.**

### 8.5 Recording and reporting of Adverse/Serious Adverse Events (non device related events)

The Investigator or appropriate site personnel will examine any subject experiencing an AE as soon as possible. The Investigator will do whatever is medically necessary for the safety and well-being of the subject. The subject will remain under observation at the Investigator's discretion. All AE's observed or reported following use of the AlcoChange device will be followed by the Investigator until resolved or until medically stabilized.

Whenever possible, the AE will be described on the appropriate CRF using standard medical terminology in order to avoid the use of vague, ambiguous, or colloquial expressions.

During the study, the Investigator or study site personnel will be responsible for querying and recording all adverse events (AEs) and serious adverse events (SAEs). Adverse events will be recorded from the date of signature of the informed consent until completion of the study at month 3 and will be evaluated by the Investigator for severity, seriousness, and relationship to study intervention, as outlined below. Untoward medical events which occur *after* signature of the informed consent *but before* use of the breathalyzer will be recorded as medical history. SAEs will be recorded from the signature of the consent form until 30 days after the last use of the breathalyzer.

Subjects will be asked at intervals throughout their assessments and again at the 3-month follow-up appointment about the occurrence of any adverse events. All AEs will be graded according to the criteria below. Additionally, the Investigator will determine the AE's relationship to the investigational device as described below. Adverse events will be followed by the Investigator until they have returned to baseline or stabilize.

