#### Serious Adverse Events: Reporting to Ethics Committees

Any submission of a SAE that is unanticipated and related to the device must also be reported to the Ethics Committee (Health Research Authority).

It is the Investigators responsibility for reporting to the HRA.

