#### 1) Anticipated Serious Adverse Events

- Variceal haemorrhage
- Spontaneous bacterial peritonitis
- Hepatorenal syndrome
- Multiple organ failure
- Death
  
- Disease progression
- Ascites
- Hepatic hydrothorax
- Non-lactobacillus bacteraemia
- Fungaemia
- Increased risk of infection
- Pre-renal failure
- Hepatic encephalopathy
- Peripheral neuropathy
- Autonomic neuropathy
- Hepatopulmonary syndrome
- Portopulmonary hypertension
- Cardiovascular insufficiency
- Hypotension
- Hepatocellular carcinoma (HCC)
- All non-HCC cancer
  
- Osteoporosis / Pathological fractures
- Hypoadrenalism
- Infertility

[figure not shown]

- Gynaecomastia
- Hyperbilirubinaemia (jaundice)
- Elevated aminotransferases / Gamma-glutamyl transpeptidase
- Hypoalbuminaemia
- Abnormalities of serum sodium, potassium, calcium, magnesium, phosphate
- Anaemia
- Thrombocytopaenia
- Leucopaenia
- Coagulopathy
- Hyperammonaemia
- Hyperlactataemia
- Necessity for patients to undergo invasive procedures (e.g. transjugular liver biopsy and haemodynamic assessment)

The above, expected SAEs (except where the outcome leads to a patient's death-see section 8.7), will not be subject to expedited reporting to the sponsor. These reports will be completed and provided to the sponsor in an agreed time frame.

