## 8.6 Responsibilities

### Principal Investigator (PI):

Checking for AEs when participants attend for treatment / follow-up.

1. Ensuring that all SAEs are recorded and reported to the Sponsor (UCL) within 24 hours of becoming aware of the event (except for those SAEs listed as expected and not requiring immediate reporting) and provide further follow-up information as soon as available. Ensuring that SAEs are chased with Sponsor if a record of receipt is not received within 2 working days of initial reporting.
2. Ensuring that AEs are recorded and reported to the Sponsor in line with the requirements of the protocol.
3. Reporting safety events to the HRA in line with national requirements.

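### Section 8.5 safety rules do not fit the added periodontal probing: early non-serious events may become medical history, and the ethics-reporting trigger covers device-related SAEs only

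*Combined protocol and SAP*

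**What the plan says.** Protocol sections 2 and 3.3 add a baseline dental examination for exploratory endpoints. The tip of a periodontal probe is placed in the gingival pocket; the examination is capped at 15 minutes and the probing force at 20-25 gm. Section 6.4 marks the blood tests and the 3-month clinic visit as standard of care but gives the dental examination no such label.

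Section 8.5 then sets these rules:

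- **Recording.** "Adverse events will be recorded from the date of signature of the informed consent until completion of the study at month 3". The next sentence says that untoward events arising after consent but before "use of the breathalyzer will be recorded as medical history". SAEs are recorded from consent until 30 days after the breathalyser is last used.
- **Relatedness.** Events are judged for relationship to the study intervention, and then: "Additionally, the Investigator will determine the AE's relationship to the investigational device as described below".
- **Ethics committee.** "Any submission of a SAE that is unanticipated and related to the device must also be reported to the Ethics Committee".
- **Anticipated SAEs.** The list includes "Non-lactobacillus bacteraemia" and "Increased risk of infection". Unless fatal, listed events "will not be subject to expedited reporting to the sponsor". Section 8.6 repeats this when it gives the PI's 24-hour duty: "except for those SAEs listed as expected and not requiring immediate reporting".

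**The concern.** The probing appears to be done for research only, so harm from it is harm from taking part in the study. The reporting rules should identify such harm as readily as harm from the device. As written, one rule can turn an early non-serious event into history, one omits procedure-related SAEs from its trigger, and one can be read as treating a procedure-related infection as expected disease.

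What is at stake is attribution and timing. Patients may have cirrhosis up to a Child-Pugh score of 7 (section 5.1), and the protocol itself anticipates coagulopathy, thrombocytopaenia and infection in them. Against that background an event caused by probing is easily put down to liver disease unless the rules prompt someone to consider the procedure. No endpoint or planned analysis is affected.

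**Working it through.** No arithmetic applies. The plan gives neither a rate of probing-related events nor a number of patients to be examined, so no expected count is offered. The check applies the written rules to three cases.

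**Case A: a non-serious event from probing, before first breathalyser use.**
1. The recording window opens at consent, which makes this an adverse event.
2. The next sentence sends events between consent and breathalyser use to medical history. The two rules conflict, and the second is the more specific.
3. Table 1 (section 6) puts the dental examination and device provision in the same baseline column and sets no order between the examination and first use of the device.
4. The same event is therefore an adverse event if the patient has already used the breathalyser, and may be medical history if not. Its classification depends on local sequence, not on its cause.
5. A serious event escapes this problem, because SAEs are recorded from consent.

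**Case B: an SAE that is not on the anticipated list and is caused by probing alone.**
1. It is recorded, and it goes to the sponsor within 24 hours.
2. The ethics rule has two conditions, and both must hold. Unanticipated: yes. Related to the device: no. The rule is not met.
3. What remains is the PI's duty in section 8.6 to report safety events to the HRA as national requirements demand. That duty is not limited to the device, but it names no trigger.

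**Case C: a serious, non-fatal infection or bacteraemia caused by probing.**
1. *Read by term*, the event matches the anticipated list. It is exempt from 24-hour reporting and goes to the sponsor on an agreed timetable. It also fails both conditions of the ethics rule.
2. *Read by purpose*, the list is introduced under Foreseeable Adverse Events as a consequence of the patients' underlying disease. An infection caused by probing then falls outside it, 24-hour reporting applies, and the event follows case B.
3. The text does not choose between these readings: it gives the reason for the list but no exclusion for events with another cause.
4. If the event is fatal, the exemption does not apply and the general 24-hour rule for SAEs returns. Section 8.7 also sends every death to the sponsor, though it gives no time limit.
5. A non-serious infection is not affected. The list covers serious events, and the separate list of anticipated non-serious events contains no infection.

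**Relatedness.** The Trial Summary and section 2.1 identify the intervention as the app and breathalyser, which favours a device-only reading of study intervention. Section 6.1.2 uses the plural in a wider sense, section 8.5 is headed as covering events not related to the device, and the device assessment is introduced as an additional one. The term is ambiguous. The definitions promised further down do not settle it: what follows is a severity scale, with no causality categories.

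**The case against.** The strongest reply is that little is lost. Every SAE is recorded from consent and reaches the sponsor, and listed ones are only later. Section 8.6 adds an HRA duty with no device limit, and gives the chief investigator or delegate a causality judgement on SAEs when no local assessment could be obtained. Nothing stops an investigator from naming probing as a cause. The CRF, the SAE form and the attached dental details were not available, and any of them might already capture procedure-related causality. All of this stands, and it keeps the point minor. It does not reach case A, because those safeguards do not say how an early non-serious event is to be classified.

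It is also fair to say that the conflict over early events is not specific to dentistry; it affects any event before breathalyser use. That is true, but probing is a study procedure that can itself cause an event in that interval.

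A reader might go further and infer three things that the documents do not support:

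- *That section 8.5 assesses relatedness to the device alone.* The first assessment uses an ambiguous term, so this is not established.
- *That a probing-related infection is definitely exempt from expedited reporting.* The stated basis of the list is the underlying disease, so exemption is one available reading, and only for serious, non-fatal cases.
- *That SAEs from probing have no route to an ethics body.* The specific trigger is not met, but the general HRA duty remains.

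**Conclusion.** The concern holds as a minor one. Two parts rest on explicit text: the conflict over events between consent and first breathalyser use, and an ethics trigger that an SAE caused by probing alone cannot meet. The third part, the anticipated list, is an ambiguity.

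The size is small. The examination is brief and low-force, serious events still reach the sponsor, and no endpoint is touched. The conclusion assumes that the probing is not routine care, which is inferred from its exploratory purpose and the missing standard-of-care label. Case A further assumes that at least some patients are probed before they first use the breathalyser, which the protocol neither requires nor excludes.

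**What to change.** Make three wording changes in section 8.5:

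1. **Recording and relatedness.** Record as an adverse event anything from consent onward that is possibly related to a study procedure, whether or not the breathalyser has been used. Ask for relationship to *the device or a study procedure (e.g. dental examination)*, with a matching CRF item if there is none.
2. **Ethics committee.** Extend the trigger to unanticipated SAEs *related to the device or a study procedure*.
3. **Anticipated SAEs.** State that the list covers only events judged due to the underlying disease.

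The cost is an amendment to the text and at most one CRF item, completed by the existing investigators. The downside is that slightly more events will be recorded or sent by the expedited route. Because the document set already contains results, the practical use is to recheck early entries filed as medical history, and to keep this wording out of the randomised trial whose feasibility this pilot is meant to inform (section 4).

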### Serious Adverse Events: Reporting to Sponsor (UCL)

#### Reportable Events

- any SAE
- any Investigational Medical Device Deficiency that might have led to a SAE if a) suitable action had not been taken or b) intervention had not been made or c) if circumstances had been less fortunate
- new findings/updates in relation to already reported events.

### Reporting Procedure

Any SAE (or occurrence listed above under "Reportable Events") that occurs during this study must be reported immediately (within 24 hours) to the sponsor's office on the following email address:

[figure not shown]

[[contact]](mailto:[contact])

Follow up information must be submitted promptly by faxing or e-mailing the updated SAE reporting forms (provided by UCL) to the sponsor office. The appropriate CRF(s) will be updated with any information collected while reviewing the SAE in a timely manner. The medical monitor is available to provide medical guidance regarding SAE reporting.

#### Serious Adverse Events: Reporting to Ethics Committees

Any submission of a SAE that is unanticipated and related to the device must also be reported to the Ethics Committee (Health Research Authority).

It is the Investigators responsibility for reporting to the HRA.

#### Foreseeable Adverse Events

Given the underlying disease state for the study population for this trial, there are multiple expected serious adverse events. For this trial, expected SAEs are presented below.

#### 1) Anticipated Serious Adverse Events

- Variceal haemorrhage
- Spontaneous bacterial peritonitis
- Hepatorenal syndrome
- Multiple organ failure
- Death
  
- Disease progression
- Ascites
- Hepatic hydrothorax
- Non-lactobacillus bacteraemia
- Fungaemia
- Increased risk of infection
- Pre-renal failure
- Hepatic encephalopathy
- Peripheral neuropathy
- Autonomic neuropathy
- Hepatopulmonary syndrome
- Portopulmonary hypertension
- Cardiovascular insufficiency
- Hypotension
- Hepatocellular carcinoma (HCC)
- All non-HCC cancer
  
- Osteoporosis / Pathological fractures
- Hypoadrenalism
- Infertility

[figure not shown]

- Gynaecomastia
- Hyperbilirubinaemia (jaundice)
- Elevated aminotransferases / Gamma-glutamyl transpeptidase
- Hypoalbuminaemia
- Abnormalities of serum sodium, potassium, calcium, magnesium, phosphate
- Anaemia
- Thrombocytopaenia
- Leucopaenia
- Coagulopathy
- Hyperammonaemia
- Hyperlactataemia
- Necessity for patients to undergo invasive procedures (e.g. transjugular liver biopsy and haemodynamic assessment)

The above, expected SAEs (except where the outcome leads to a patient's death-see section 8.7), will not be subject to expedited reporting to the sponsor. These reports will be completed and provided to the sponsor in an agreed time frame.

## 2) Anticipated Non-serious Adverse Events

- Oedema
- Bruising
- Hair loss
- Amenorrhoea
- Hair loss
- Nausea
- Vomiting
- Constipation
- Diarrhea
- Headache

The above, expected AEs, will be recorded in the medical notes only.

## Severity Grading for Adverse Events

The Investigator will assess all AEs according to the criteria described below. The severity of an event should be graded into one of three classes which describe the clinical severity of the event as it occurred.

The three classes of severity are:

- Mild / Grade 1: does not interfere with daily living and no medications are needed to relieve event;
- Moderate / Grade 2: somewhat interferes with daily living or medications needed to relieve event;
- Severe / Grade 3: incapacitating, activities of daily living are prohibited because of the event.

[figure not shown]

## 8.6 Responsibilities

### Principal Investigator (PI):

Checking for AEs when participants attend for treatment / follow-up.

1. Ensuring that all SAEs are recorded and reported to the Sponsor (UCL) within 24 hours of becoming aware of the event (except for those SAEs listed as expected and not requiring immediate reporting) and provide further follow-up information as soon as available. Ensuring that SAEs are chased with Sponsor if a record of receipt is not received within 2 working days of initial reporting.
2. Ensuring that AEs are recorded and reported to the Sponsor in line with the requirements of the protocol.
3. Reporting safety events to the HRA in line with national requirements.

### Chief Investigator (CI) / delegate or independent clinical reviewer:

1. Clinical oversight of the safety of patients participating in the trial, including an ongoing review of the risk / benefit.
2. Using medical judgement in assigning seriousness, causality and expectedness of SAEs where it has not been possible to obtain local medical assessment.
3. Reporting any Incident to the MHRA as required by the protocol and regulatory requirements.

### Sponsor (UCL):

1. Central data collection and verification of AEs and SAEs according to the trial protocol.
2. Reporting safety information to the CI, delegate or independent clinical reviewer for the ongoing assessment of the risk / benefit according to the Trial Monitoring Plan.

## 8.7 Notification of deaths

- All deaths will be reported to the sponsor irrespective of whether the death is related to disease progression, the AlcoChange device, or an unrelated event.

## 10 DATA HANDLING

### 10.1 Data collection tools and source document identification

#### Source Data

The source data to be accessed in this study will be patient demographic data, past medical history relating to alcohol use, blood tests as SOC, saliva and stool sample laboratory results, dental examination results. This data will be entered into the study specific Case Report Form (CRF) by the research team. Questionnaires (SF36 and SUSTAINS) will be considered source.

#### Case report forms

Case report forms (CRFs) will be used to record data from baseline and end of study (3-month) assessments as above. The CI will be responsible for keeping records of all participating patients (sufficient information to link records e.g., CRFs, hospital records and samples), all original signed informed consent forms and copies of the CRF pages.

#### AlcoChange Device Data

In this study, patients will enter personal data via the device, which will initially be stored on their own mobile phones. On availability of an internet connection, the data will be synchronised onto a centralised server hosted in a secure location which is NHS compliant.

### 10.2 Data handling and record keeping

Patients will enter data on a routine basis during the study period, using the AlcoChange app that runs on Android or iOS operating systems. All data entered by the patients on their mobile phones will be transmitted to the 'CyberLiver' data platform through a web service that is securely made available only to the AlcoChange app over a secure HTTPS channel.

All patient identifiable data will be encrypted and stored in the database. The CyberLiver Platform database will be hosted on an NHS compliant environment.

[figure not shown]

Configuration and specification of the secure server is as follows;

Baseline Virtual Machines (VM) :2 x vCPU with 100Gb premium disk space (RAM, additional vCPU cores and extra disk space would be added as per requirement)

Failover & Recovery mechanisms will be put in place with high availability virtual machines having built in redundancy and automated restart capability of VM's on a new physical host within the cluster, in the event of a hardware or Hypervisor failure on the host.

Host-based backups would be performed nightly using the industry leading software. Backups of the VM container will be stored on-site unless otherwise specified, to a 14 point retention period; backup disk space up to 50% of allocated disk.

A Virtual Machine would be used which would ensure that dedicated physical disks assigned to virtual database machines ensuring disk IO performance matches or better than that found on physical machine databases.

The servers will be secure and segregated from all other client databases and/or applications within a dedicated VLAN running under a dedicated operating system.

High availability recovery will be in place within minutes in the event of critical failures.

Server patching, updates, application and database administration will all be managed by the CyberLiver team.

Token based secure 2-Factor Authentication will be in place in addition with N3 connectivity.

The platform will also have a secure web-based portal that will be accessible only by the alcohol liaison team and the research team. Unique sets of credentials for each user requiring access will be provided. All users will only have read-only access to patient data. All user actions will be monitored with audit logs of every action performed by the users.

